### Procedures

#### Mentor Training

For overall schematic of the procedures for mentor training and administration of the intervention see Figure 2. Mentors will receive six hours of training with trained doctoral-level research study personnel in the UCLA Pediatric Pain Program prior to working with mentored participants.

##### Training manual

The training material will include background on chronic pain disorders and rationales for pain self-management; specific goals of the program and the mentor's role; how to present information about pain and pain-related behaviors; strategies drawn from CBT to reinforce positive thinking and to challenge negative statements; guidelines for building the mentoring relationship, dealing with difficult issues (e.g., depression, suicidality, or other potential emergencies such as disclosure of abuse), and ending the interactions. Mentors will be given a written manual presenting all the material in detail for their ongoing reference. The mentors' specific objectives will be to provide information about pain, pain-related behaviors, thoughts, and feelings, and the nature of recommended treatments, as well as to alleviate the subject's sense of isolation by giving him or her the opportunity to discuss his or her pain condition with someone who has shared the experience; to enhance and reinforce the subject's sense of self-efficacy to manage the pain condition; and to encourage the mentored participant to participate actively in the recommended pain self-management skills building therapy. Mentors will be trained in conversational strategies to help them meet the objectives without being overly directive (see details below).

##### Peer Mentor Training

A postdoctoral psychologist ([name]) together with other research staff trainers will begin conducting training when at least six (6) peer mentors have been identified and recruited. Training will consist of one six-hour session including all mentors, which will include the following: 1) Review of slide presentation and rationale for learning pain self-management, as well as the contribution of biological, psychological, and social factors to the pain experience; 2) demonstration and practice of some basic skills to use in working with the mentored participants; 3) review of the manual; outline of the format and required elements for each call; 4) participation in role-playing exercises in pairs to learn ways of presenting didactic information, supporting positive statements, and responding to questions posed by the mentored participant; 5) participation in question development and topic-starter exercises; 6) participation in troubleshooting exercises to suggest ways of addressing particular problems; 7) review of call formats, reporting requirements and detailed discussion of emergency situation procedures.

Prior to working with actual study patients, the best surrogates for the mentors to practice their new skills with are their fellow mentors, who will all be adolescents with resolved or ongoing recurrent pain problems, whose recent experiences have been similar to those of the mentored participants. Each mentor will participate in several different role-playing exercises during training, in which the mentors will break into pairs and improvise conversations that will occur between mentor and mentored participant. For example, they might be told: "One of you will be the mentored participant who has been to a couple of therapy sessions, but is feeling discouraged, like therapy isn't working and probably nothing is going to help. Talk to your partner and choose a specific therapy. Make up a conversation between the two of you, in which the mentored participant wants to give up on therapy and the mentor responds to those feelings. Remember what you have learned about cognitive-behavioral principles in thinking about what the mentor should say." These mock conversations will be observed and critiqued by trainers. Each mentor will be assigned to no more than three mentored participants at any one time; some mentors will only work with one mentored participant during some cycles, to ensure they can take on a mentored participant if one of the group becomes ill or has another emergency. (Additional mentors may be trained during the intervention period if needed due to attrition or higher than anticipated subject enrollment.) During the period of active mentorships (about 18 months), mentors will meet monthly with the research team to review guidelines, provide feedback, and discuss problems that may arise. Mentors will participate in the ongoing iterative process of reviewing and refining the protocol after each cycle.]

##### Emergency Support

Particular attention will be paid to the rare emergency situations that may arise in the course of mentor-mentored participant conversations, such as disclosure of domestic abuse, suicidal or self-harm intent. Procedures will be discussed at length in the training session. The mentor will be given detailed instructions about how to behave in these specific situations. In addition, parents of peer mentors will agree to be reachable at all times either in person or by phone in case of emergency. Following any such occurrence, the mentor will be given immediate counseling by the PI or a monitoring research team member, and will be referred for extended counseling if s/he suffers resulting distress. In addition, all calls will be monitored directly by a member of the research team trained in emergency procedures (i.e. for abuse, suicidality disclosures, etc.) and recorded using digital audio recorders.

### Mentored/Control Subject Assessment

For an overall schematic of the assessment schedule for mentored participants and controls, please see Figure 1. The baseline and 2-month follow up assessments will consist of a semi-structured interview and self-report questionnaires. The final assessment at four months from baseline consists only of a self-report questionnaire packet. For the mentored participants, the study will consist of baseline assessment, two months of active intervention, immediate follow-up assessment at the end of intervention, and then a final assessment at four months from baseline. For the controls, the study will consist of the baseline assessment, two months of usual care, immediate assessment, and then follow-up assessment at four months.

**Figure 1 F1:**
[figure not shown]
**Procedural flow chart for mentored participants and controls**.

**Figure 2 F2:**
[figure not shown]
**Procedural flow chart for mentors**.

Mentored participants and control subjects will be called once per week during the intervention/usual period (first 8 weeks of the study) by trained research study personnel to assess use of recommended therapies, medications, and additional non-physician recommended therapies. During these weekly assessments, research staff will also assess for the presence of any suicidal ideation/intent. In addition to monitoring suicidality, several other assessment measures focused on pain, disability, and negative affect will be completed weekly by mentored participant and control subjects online using a web-based program from a computer in their homes.

### Intervention

Each mentored participant will be assigned to a peer mentor. Each mentor will work with no more than three subjects at one time; once all mentors have been assigned one to three subjects, recruitment will stop until the intervention cycle concludes. Cycles may be staggered depending on recruitment and mentor availability.

Each cycle will consist of 10 sessions of 30-60 minute phone calls conducted over a period of eight weeks. The mentor and mentored participant(s) will have two sessions per week for the first two weeks, and one session per week for the remaining six weeks. Current literature supports the use of an expanding-interval schedule of interventions (compared to a massed (single session) or uniform-interval schedule) with evidence that the expanding schedule may help to attenuate long-term recurrence of negative emotions [37]. Phone calls will take place on a secured, monitored conference call line so that no participants will exchange personal contact information. The time of all phone meetings will be scheduled by the research staff, based on availability of mentor and mentored participant(s) and will remain at a fixed time each week. Mentoring sessions will occur only during the scheduled times and mentored participant-mentor contact outside of the mentoring sessions will be specifically prohibited. During each session, participants will also be viewing a slide presentation at the time of the conference call, so that didactic information can be presented. This presentation has been developed by doctoral-level research staff. As previously mentioned, to ensure safety of all participants, a member of the research team will be monitoring all telephone calls. This individual will facilitate the discussion, only if necessary, as well as intervene in any potential safety concerns (e.g., discussion of suicidal ideation) or inappropriate behavior (e.g., bullying).

In an effort to increase adherence, mentored participants will be informed that if they miss two consecutive mentoring sessions, or miss three sessions total over the course of the intervention for non-emergency reasons, they will be removed from the study. Additionally, peer mentors who miss two mentoring sessions (for non-emergency reasons) will be removed from further participation as a mentor. Mentored participants will then be reassigned to a new mentor for the remaining sessions.

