**Methods:**

This protocol will recruit adolescents ages 12-17 with chronic pain and randomly assign them to either peer mentorship or a treatment-as-usual control group. Mentored participants will be matched with peer mentors of similar age (ages 14-18) who have actively participated in various treatment modalities through the UCLA Pediatric Pain Program and have learned to function successfully with a chronic pain disorder. The mentors will present information to mentored participants in a supervised and monitored telephone interaction for 2 months to encourage participation in skill-building programs. The control group will receive usual care but without the mentorship intervention. Mentored and control subjects' pain and functioning will be assessed at 2 months (end of intervention for mentored participants) and at 4 month follow-up to see if improvements persist. Measures of treatment adherence, pain, disability, and anxiety and depression will be assessed throughout study participation. Qualitative interviews for mentors, mentored participants, and control subjects will also be administered.

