##### Primary Analyses

The primary outcomes are adherence (percent of sessions attended, percent of home exercises completed). The primary analysis method is repeated measure analysis of variance (ANOVA) between the two groups or the non parametric equivalent (Friedman procedure). We will subtract baseline value from the 2- and 4-month assessment values and use residualized change scores from baseline as the outcome. We will use the Tukey-Fisher criteria for post hoc mean/median comparisons under the ANOVA or Friedman model. The same methods will be used for the analyses on NRS and FDI scores.

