##### Attrition

We will compare attrition rates between the two treatment groups and compare demographics and baseline values of FDI and other measures of dropouts to non-dropouts. If dropouts are random, then the results are unbiased. If dropouts are not at random, we will comment on the direction and magnitude of potential biases.

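### Mentored participants who miss mentoring calls are removed from the study: a post-randomisation exclusion that can act in one arm only and is probably related to the primary outcome

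*Protocol article*

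**What the plan says.** The Intervention section sets out 10 mentoring calls: "Each cycle will consist of 10 sessions of 30-60 minute phone calls conducted over a period of eight weeks". A mentored participant faces removal "if they miss two consecutive mentoring sessions", or on a cumulative count: those who "miss three sessions total over the course of the intervention for non-emergency reasons, they will be removed from the study". The same paragraph gives mentors who miss calls a narrower consequence: they "will be removed from further participation as a mentor".

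For the other arm, the Abstract (Methods) says: "The control group will receive usual care but without the mentorship intervention". Staff telephone contact is common to both arms (Mentored/Control Subject Assessment): "Mentored participants and control subjects will be called once per week". No removal rule is attached to missing those staff calls.

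Under Primary Analyses: "The primary outcomes are adherence (percent of sessions attended, percent of home exercises completed". The Measures section records adherence on a tracking form that counts visits and missed appointments with the clinical team. NRS and FDI scores are to be analysed by the same methods.

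The Attrition section compares attrition rates between arms and compares dropouts with non-dropouts on demographics and baseline values. It adds: "If dropouts are random, then the results are unbiased". Otherwise the authors will comment on the direction and size of possible bias.

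**The concern.** The sanction as written takes the participant out of the study, not merely out of the calls. The contrast with the mentor rule in the same paragraph makes it hard to read as loose wording. Controls cannot trigger it, so it is an exclusion after randomisation, in one arm, driven by behaviour after randomisation.

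That behaviour is failing to turn up for scheduled sessions, and the primary outcome is whether adolescents attend their recommended therapies. If the two go together, the mentored adolescents who remain are a selected, more compliant group, compared with an unselected control group. The rule can act early: with two calls a week in the first two weeks, two consecutive misses can fall within one week.

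At stake is the randomised comparison behind Aims 3 and 4. A later analysis plan cannot repair this fully, because it cannot supply 2- and 4-month outcomes that were never collected.

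**Working it through.** **Inputs from the protocol.** 10 calls; removal at two consecutive or three total misses; rule possible in the mentored arm only; 1:1 allocation; two-sided alpha 0.05; 29 per group (Sample Size Determination); 32-48 mentored participants expected.

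**Inputs assumed.** The share *q* of the mentored arm removed and the correlation *ρ* between mentoring attendance and therapy adherence. The protocol gives neither, so both are varied.

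**The plan's own figure.** The protocol gives no expected number of removals to reproduce. Its one power figure, 29 per group, serves here only as a trial size. The usual two-sample formula does not return it: 2 × (1.9600 + 0.8416)² / 0.52² = 58.05, so 59 per group. That is a separate matter, and nothing below rests on it.

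**Step 1: how many the rule could remove.** Suppose each call is missed independently with probability *p*, and every miss counts. A participant stays with no miss, one miss, or two non-adjacent misses. There are 45 − 9 = 36 non-adjacent pairs among 10 calls, so

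P(removed) = 1 − [(1−p)¹⁰ + 10p(1−p)⁹ + 36p²(1−p)⁸].

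For p = 0.10: 1 − [0.3487 + 0.3874 + 0.1550] = 0.109.

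| Per-call miss probability | Share removed |
|---|---|
| 5% | 2.6% |
| 10% | 10.9% |
| 15% | 23.5% |
| 20% | 38.3% |

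A range of 10-30% is therefore possible under modest miss rates, but a much smaller share is possible too.

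**Step 2: spurious shift in adherence with no true effect.** Treat attendance and adherence as standard normal with correlation ρ, and remove the lowest share q on attendance. The mean adherence of those left rises by

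shift = ρ × φ(z_q) / (1 − q), with z_q the q-quantile.

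For q = 0.20, φ(−0.842) / 0.80 = 0.280 / 0.80 = 0.350, so at ρ = 0.5 the shift is 0.175 SD.

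**Step 3: type I error.** 4,000 simulated trials per setting, two-sided t-test, n randomised per arm, removal in the mentored arm only.

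| q | ρ | Shift (SD) | Type I error, 29 per arm | Type I error, 48 per arm |
|---|---|---|---|---|
| 10% | 0 | 0 | 4.6% | 5.0% |
| 10% | 0.3 | 0.058 | 5.1% | 6.3% |
| 10% | 0.5 | 0.097 | 5.5% | 7.8% |
| 10% | 0.7 | 0.136 | 7.6% | 10.1% |
| 20% | 0 | 0 | 4.5% | 4.6% |
| 20% | 0.3 | 0.105 | 6.2% | 8.0% |
| 20% | 0.5 | 0.175 | 8.7% | 12.9% |
| 20% | 0.7 | 0.245 | 14.0% | 20.2% |
| 30% | 0 | 0 | 4.6% | 4.6% |
| 30% | 0.3 | 0.149 | 8.1% | 10.3% |
| 30% | 0.5 | 0.248 | 13.6% | 19.0% |
| 30% | 0.7 | 0.348 | 23.2% | 36.2% |

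The simulation error near 5% is √(0.05 × 0.95 / 4000) = 0.34 percentage points, so the rows at ρ = 0 agree with 5%. A second run at 29 per arm, deleting the lowest attenders, gave 10.0% at q = 20%, ρ = 0.5 and 24.0% at q = 30%, ρ = 0.7. The shift does not shrink with sample size, so the error rate grows with enrolment.

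**Step 4: if nobody is removed.** With q = 0 the shift is 0 and type I error stays at 5%.

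**The case against.** The strongest reply is that missed mentoring calls are not missed therapy. The rule counts telephone calls with a peer, while the tracking form counts clinician visits. The documents give no figure linking the two, and at ρ = 0 the bias is nil. This stands. A reader might infer that the rule strips out the poorest adherers as a matter of fact; the text supports only that they are likely to be poorer adherers.

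Four other inferences are tempting and also go too far.

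- *Removed participants drop out of a complete-case analysis.* The Primary Analyses section names repeated-measures ANOVA or Friedman and does not state the analysis population or how missing values are handled. A protocol article may leave that to the analysis plan. Weekly tracking, NRS and FDI in weeks 1-8 also yield data before removal. What cannot be filled in is whatever was not collected afterwards.
- *Feasibility is overstated because non-attenders leave the denominator.* No denominator is stated, and attrition rates are to be compared between arms, so removals can be counted.
- *The Attrition sentence on random dropout is wrong.* It is a correct conditional. The difficulty is that the Intervention section makes some dropout depend on attendance by rule.
- *The shift can be measured against the planned effect of 0.52.* That is an FDI effect size; the shift above is in adherence, for which the protocol says no effect sizes were available.

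The planned outcome is also residualized change from baseline, which may absorb part of a stable difference in compliance that the calculation leaves in. The sentence may be meant mainly as a warning to encourage attendance, but it states a consequence, and nothing says that follow-up continues. Finally, this is an exploratory pilot with a larger trial to follow. That tempers the consequence without removing it, since between-arm tests are planned.

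**Conclusion.** The concern holds in this form: the protocol prescribes a one-arm, attendance-triggered removal from the study after randomisation, the trigger is probably related to the primary outcome, and nothing stated keeps removed participants under follow-up. The adherence comparison can then favour mentoring with no true effect.

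The illustrative size, for adherence alone, is 0 to 0.35 SD for 10-30% removed and correlations of 0 to 0.7; at correlation 0.5 it is 0.10 to 0.25 SD. Type I error at 29 per arm runs from 5% to about 23-24%, and is about 9-10% at 20% removed and correlation 0.5. These figures rest on assumed removal shares and correlations, normal variables and outcomes not adjusted for baseline.

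Pain and FDI may be affected as well. A reader might infer that they too would be biased towards mentoring, but the documents do not allow size or direction to be stated: adolescents who feel better may also stop attending. Nor is the defect the lack of a matching rule for controls, since they have no mentoring calls to miss. The defect is the loss of follow-up.

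**What to change.** Reword the sanction so that any rule for ending mentoring ends only the mentoring calls. What that rule should be is not a matter for this point. Keep every randomised participant in the weekly tracking and in the 2- and 4-month assessments already scheduled for both arms. State that all randomised participants are analysed in their assigned arm, using all data collected. The choice of model and any sensitivity analysis for remaining missing values can be left to the analysis plan.

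The cost is a short amendment with matching participant information, and somewhat more follow-up effort for adolescents who have stopped the calls. The estimated effect may also be smaller because non-attenders stay in, but it will then be the effect of being assigned to mentoring.

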### Ethics

All participants (mentors, mentored participants and control subjects) provide voluntary written informed assent or consent with full knowledge of study participation requirements and potential risks. When required for participants who are legal minors, voluntary written informed parental consent is also requested. All participants are informed that any decision about participation will have no effect on their relationship with UCLA or their medical care at UCLA. This study was approved by the UCLA Institutional Review Board.

### Measures

#### Primary Outcomes

1. ***Adherence ***to recommended therapies, use of additional therapies, and medication use will be evaluated using the Treatment Services Tracking Form - a measure designed specifically for use in this study to assess number of visits and missed appointments with team clinicians each week. This form is administered verbally by research staff. Treatment adherence reported by participants is then corroborated with reports from program clinicians.

2. ***Pain: ***Demographics questionnaire and pain level as indicated on a body diagram and several Numerical Rating Scales (NRS; 0-10 scale) [38] to represent a continuum from no pain at all to the worst pain possible. The NRS has been established and widely used as a valid and reliable measure of pain intensity.

3. ***Functioning:***

a. Self-perceptions of difficulty in physical and psychosocial functioning due to physical health as measured on the Functional Disability Inventory (FDI) [39], a well-validated 14-item self-report questionnaire with a five point scale that asks children the level of difficulty they have with typical daily activities.

b. Self-perceptions of health and functioning as measured on the Children's Health Questionnaire (CHQ), a quality of life instrument designed for use with children age 5 and above. The CHQ measures 14 unique physical and psychosocial health concepts (e.g., physical functioning, limitations in school, self-esteem, mental health, family functioning) that can be analyzed and reported separately or combined to derive an overall physical and overall psychosocial score. There are 87 items [40].

#### Secondary Outcomes

4. ***Anxiety and Depressive Symptoms:***

a. The Child Anxiety Sensitivity Index (CASI), an 18-item scale for measuring anxiety sensitivity. Children rate each item (e.g., It scares me when I feel like I am going to throw up) on a scale ranging from *none *to *a lot *[41].

b. Symptoms corresponding to selected *DSM-IV *anxiety disorders and depression, as assessed by the 47-item, 4-point, Revised Child Anxiety and Depression Scale (RCADS) [42,43].

c. Suicidal ideation will be assessed using a question from the Beck Depression Inventory - 2^nd^ edition (BDI-II) to assess suicidality [44].

For a complete list of measures and time points at which they are administered for each subject group, please see Tables 1 and 2.

**Table 1 T1:** Timetable for study participation for mentored and control subjects

	TIME PERIOD					
	
STUDY PARTICIPATION FOR ADOLESCENT MENTORED AND CONTROL SUBJECTS	Baseline	Week 1-2	Week 3-8	2-month follow-up	Weeks 9-16	4-month follow-up
Measures						

Demographics, NRS & body diagram	X	X	X	X		X

FDI	X	X	X	X		X

CASI	X			X		X

RCADS	X			X		X

BDI-II suicidality	X	X	X	X		X

Treatment tracking	X	X	X	X		X

Interview	X			X		

Estimated Time Required for Study Participation	76 MINS	140-260 MINS	240-420 MINS	86 MINS		56 MINS

**Table 2 T2:** Timetable for study participation for peer mentors

	TIME PERIOD				
**STUDY PARTICIPATION FOR ADOLESCENT PEER MENTORS**	**Months 1-2**	**Months 3-4 (first cycle)**	**Month 5 (break)**	**Months 6-18 (cycles 2-5)**	**Month 19**

Training Sessions	X				

Mentorship Phone Talks and Debriefings		X		X	

Questionnaire Packet	X				X

Assessment and Review Meetings		X		X	

Interview	X				X

Estimated Time Required for Study Participation	7.2-7.8 HOURS	9 HOURS		36 HOURS	70-100 MINS

